## Background:

Leprosy is a chronic infectious disease of the skin and nervescaused by the intracellular pathogen *Mycobacterium leprae*. Itis characterized by a spectrum of clinical forms depending onthe host's immune response to *M. leprae*. Leprosy may be complicated by inflammatory reactions. Type 1 (reversal) reactions (T1R), common in borderline formsof leprosy, are due to delayed-type hypersensitivity and anincrease in CMI to *M. leprae* antigens.

Preventing peripheral nerve damage is a major challenge in leprosy. Nerve damage occurs commonly in Type 1 reaction (T1R), and may be irreversible if not treated early and adequately1 2 3. Acute neuritis may also occur without the skin lesions of Type1 reactions.4

Type1Reactions are characterized by acute granulomatous inflammation that can produce destruction of nerves even to the extent of causing caseous necrosis of the nerve tissue and irreversible paralysis. The swelling of the nerves due to sudden increase in inflammatory cells and oedema within an unyielding perineurium produce ischaemia and transient paralysis5.

Corticosteroids are the accepted method of treating nerve function impairment and reactions in leprosy6. The effectiveness of steroids compared to placebo is uncertain.7 Corticosteroids have been used since 1950 for treating reversal reactions8 9. They are used because the TIR skin and nerve lesion show inflammation. Type 1 reactions, are due to delayed-type hypersensitivity and anincrease in CMI to *M. leprae* antigens. A transient increase in the CMI response to antigens of *M.leprae* has also been reported lasting for weeks and then declining10. Prednisolone both decreases inflammation and suppresses the CMI.

Steroid courses used in the 1950s and 1960s were usually short and low dose, although by the 1980s longer courses and higher doses were being recommended.[[1]](#endnote-2)

Currently, standardized regimens, e.g. Prednipac (packaged course of steroids starting at 40 mg per day and reducing over 12 weeks), are used under field conditions and for out patients as they have been found to be relatively safer. 12 However a recent multi centre, double blind, randomized controlled trial showed a clear superiority of longer duration steroids for 20 weeks compared to a 12-week regimen17. This study will incorporate the current evidence on duration of treatment and use a course of prednisolone tapered over 20 weeks.

Treatment with corticosteroids improves both reactional skin lesions and neuritis. A retrospective study reported only a 50% improvement in clinical signs and symptoms of reactions involving nerves13, while other studies have reported improvement in nerve function of 60% to 70%.14 However upto 30% of patients with type 1 reactions or nerve function impairment may not improve with prednisolone.15

Patients treated with the standardized steroid course often require additional steroids while the dose is tapered – a recent trial conducted in Nepal showed 50% of patients treated with a 12 week prednisolone regimen required further steroids.16 The need for additional steroids prolongs the duration of steroid treatment and the total amount of steroid used. Another problem with using corticosteroids is the associated adverse effects.8 Concerns over such adverse effects of steroids used under field conditions have lead to pressure to keep the dose and duration to a minimum.17

The risks of adverse effects with standardized regimens of corticosteroids for the treatment of leprosy reaction in the field have been described.18

The adverse effects associated with corticosteroid therapy can be classified into minor such as moon face, fungal infections, acne and gastric pain. The major adverse effects being gastric ulcer, glaucoma, diabetes, hypertension, osteoporosis, cataract and a range of psychiatric disturbances ranging from mood alterations to psychosis. Besides these life-threatening infections can also occur. The risk of minor adverse effects while being on prednisolone was 16 % and 2% for major side effects. Dermatological side effects namely moon face, acne and fungal infections were seen in 6.5 % of patients on prednisolone .19

There is an urgent need for an adjunct to steroids in the treatment of type I reactions because:

1. 30-50% of patient with acute neuritis do not show neurological improvement when treated with the standard steroid regimens.
2. There is flare-up of skin lesions while steroid doses are tapered down.
3. Some patients require prolonged courses of steroids and become steroid-dependent.
4. Alternative treatments are needed for patients with contraindications to corticosteroids
5. Alternative treatments are needed for patients with severe neuritis who do not improve on steroid treatment.

Azathioprine is an immuno suppressant that has been used in other immune mediated diseases both as monotherapy and in combination with prednisolone as a steroid-sparing agent.20 It is metabolized to mercaptopurine by the enzyme thiopurine methyltransferase. It is widely used for organ transplant recipients and to treat a number of autoimmune conditions, usually when corticosteroid therapy alone provides inadequate control. 21

A recent trial conducted in Nepal using a three-month course of Azathioprine along with Prednisolone showed that addition of Azathioprine reduces the corticosteroid requirement for treatment of type 1 reactions. Although the clinical outcomes were similar for patients treated with either the prednisolone/azathioprine combination or prednisolone alone, the overall dose of prednisolone was less in those on the combined regimen.16 One of the shortcomings of the Nepal study was that the azathioprine was not used for a long enough duration.

Adverse effects due to azathioprine may occur in upto 15% of patients.21 The commonest adverse reactions that occur with azathioprine are nausea and vomiting and mucosal ulcers, occurring in 60% of patients.22 Azathioprine also causes significant bone marrow suppression (upto 5%) and can potentially cause leucopenia (3.8%), thrombocytopenia (2%) and even pancytopenia (0.4%).23 There may be an increased risk of infections and different malignancies. Pancreatitis, skin rashes and drug fever have been reported on rare occasions.24 Use of azathioprine in pregnancy has shown that the placenta may act as a barrier to its passage and current evidence of safety in pregnancy is reassuring.25, 26

## Introduction:

## Study Aims

The primary aim of this study is to compare the neurological outcomes in patients with type 1 reactions and recurrent type I reactions in skin lesions, when they are treated with either Azathioprine in addition to a 20-week course of prednisolone or prednisolone alone.

The objectives of the study are: -

1. Improves dermatological outcomes in Type 1 reactions.

2. Improves neurological outcomes in Type 1 reactions and neuritis

3. Reduces the recurrence rate (i.e. requirement for further treatment with steroids) in patients with T1R and neuritis.

4. To compare the effectiveness of different duration of treatment with Azathioprine in T1R and neuritis.

***Methods***

## Study design and setting

This study is a randomized double blind controlled clinical trial with continuous enrollment of individuals into 4 arms of the study.

The participating centres are:

- TLM hospital Faizabad, (UP)
- TLM Hospital Shahdara (Delhi).
- TLM Hospital Purulia (West Bengal)
- TLM Hospital, Champa

The study will compare Azathioprine when used with prednisolone against prednisolone used alone, for the treatment of acute neuritis and recurrent reactional skin lesions.

Azathioprine will be used at three durations of 24 weeks, 36 weeks and 48 weeks. All patients will complete 48 weeks of treatment comprising Prednisolone (20 weeks standard therapy) + Azathioprine/Placebo.

Clinical measurement of nerve function and skin appearance will be used to determine the outcomes.

##

## Identification of eligible patients

Eligible patients will be identified from among the patients undergoing regular skin examination, and nerve function assessment at the physiotherapy units in the four participating TLM hospitals.

The physiotherapy unit at each of the participating hospitals will flag all patients presenting with new nerve function impairment or recurrent reactional skin lesions, these flagged patients will be “fast tracked” and will taken to the designated medical officer for the study.

The patient would then be screened for eligibility; the pre-treatment assessment form will be filled in, if found eligible would be offered a choice of participating in the study subject to the patient consenting to participate in the study.

#### Determining the eligibility for the study

All patients with a diagnosis of leprosy (whether paucibacillary or multibacillary) and evidence of recent onset neuritis or recurrent skin lesions in type 1 reactions will be included in the study as long as he/she satisfies the inclusion criteria and does not have any absolute exclusion criteria listed in table 1. For the purpose of this study neuritis will be defined as: -

- Spontaneous nerve pain, paraesthesia or tenderness (or)
- New sensory or motor impairment of recent onset detected by voluntary muscle testing and sensory testing (or)
- Mixed sensory and motor signs.
  - The MDT status (past or current) of the patient does not affect eligibility provided they have recent neuritis or recurrent reactional skin lesions.
- Patients who are already on steroids (started within the past one month) will be included if they present with new nerve damage or fresh evidence of neuritis while on treatment with steroids.

The local MO decides whether the patient can be included in the study.

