#### Inclusion Criteria:

Patients with acute (< 6 months) neuritis with or without accompanying type 1 reaction or recurrent reactional skin lesions without neuritis.

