## Patient outcome measures

### Primary outcomes

1. **Recovery of nerve function**

- Absolute improvement in nerve function as measured by Voluntary Muscle testing (one point improvement in VMT score) and Sensory testing (two point improvement in ST score) using standard methods as defined in the field manual.

1. **Recurrence of neuritis during or after treatment**

- Recurrence of neuritis is defined as a new nerve function impairment presenting in the form of a decrease in VMT score by one point and an ST score by more than 2 points either during the study period or during the follow up period and present for two consecutive testings.

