### *Definitions:*

### *Neuritis*: A leprosy patient is diagnosed as having neuritis when he/she has any of the following:

- Spontaneous nerve pain, paraesthesia or tenderness (or)
- New sensory or motor impairment of recent onset detected by voluntary muscle testing and sensory testing (or)
- Mixed sensory and motor signs

*Acute Neuritis*: For neuritis to be acute it has to have appeared within the last six months (defined either by previous testing or patients history of new sensory or motor loss)

*Type1Reaction* (T1R) is defined as the development of an acute or subacute inflammation affecting the skin and / or nerves occurring in leprosy, due to a hypersensitivity to *M.leprae* antigens, resulting in a change in the appearance of skin lesions and / or nerve damage and disability.

A T1R is diagnosed when a patient has erythema and edema of skin lesions. There may be accompanying neuritis and edema of the hands, feet and face. The skin signs are obligatory; the nerve and general signs optional.

*Acute T1R* is defined as the presence of erythematous and raised skin lesions with or without evidence of neuritis of less than 6 months duration prior to presentation.

*Recurrent reactional skin lesions* are defined as newly erythematous lesions that have either developed off steroids or whilst on steroids.

*Silent Neuropathy (SN)*

A patient is defined as having silent neuropathy when he/she has sensory and/or motor impairment of recent onset (< 6 months duration) in an area innervated by one or more nerve without signs of a reaction (RR or ENL) or nerve pain and with or without tenderness.

*Sensory Impairment:* A patient is diagnosed as having sensory impairment in any of the following situations: the monofilament threshold was increased from the normal threshold (2gm/purple for the hand and 10gm/orange for the foot) by three or more levels (filaments) on any site, OR two levels on one site AND at least one level on another site, or one level on three or more sites for one nerve.

*Motor Impairment:* A patient will be diagnosed as having motor impairment if the VMT score for any muscle is four or less on the 0-5 (modified) MRC scale.

*Worsening of skin lesions:* is defined as occurrence of a fresh episode of acute skin inflammation with or without edema while enrolled in the study.

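### Neuritis shown only by nerve pain, paraesthesia or tenderness qualifies under the eligibility text but has no path in the recruitment flow chart, and patients without a baseline deficit dilute the recovery outcome

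*Protocol*

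**What the plan says.** **Text that admits the patient.** In the Protocol, *Determining the eligibility for the study* defines neuritis by alternatives. The first is "Spontaneous nerve pain, paraesthesia or tenderness (or" and the second is "New sensory or motor impairment of recent onset detected by voluntary muscle testing and sensory testing (or". *Definitions* repeats the list and makes any one item enough: "A leprosy patient is diagnosed as having neuritis when he/she has any of the following". *Inclusion Criteria* takes "Patients with acute (< 6 months) neuritis with or without accompanying type 1 reaction or recurrent reactional skin lesions without neuritis" and does not mention nerve function impairment.

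**Text that has no place for the patient.** The *Flow Chart for Recruitment* starts from nerve function impairment or recurrent reactional skin lesions. Its entry condition is impairment of under six months or such lesions. It shows no box for pain, paraesthesia or tenderness alone. Under *Identification of eligible patients*, the physiotherapy units "will flag all patients presenting with new nerve function impairment or recurrent reactional skin lesions". In *Definitions*, neuritis counts as acute when it appeared within six months, "defined either by previous testing or patients history of new sensory or motor loss".

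**Who applies the rule.** "The local MO decides whether the patient can be included in the study", at each of four hospitals.

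**What is measured.** The first item under *Primary outcomes* is "Absolute improvement in nerve function as measured by Voluntary Muscle testing (one point improvement in VMT score", together with a two-point gain on sensory testing. The second is recurrence of neuritis, defined by a fall in those scores. *Statistical analysis* applies the intention-to-treat principle to the primary outcome.

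**The concern.** A patient with a tender nerve, normal function tests and no recurrent skin lesion is eligible by the written criteria and has no way in by the flow chart. Staff cannot follow both. If one hospital works from the text and another from the chart, the trial population depends on the site, and the published result has no clear population to apply to.

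The choice also affects the analysis. Recovery is a gain in muscle or sensory score, and a patient who starts at the top of both scales has no gain to make. If such patients are counted under intention to treat, they enter as non-recoveries whatever they are given. That lowers the recovery rate in every arm and narrows the difference between arms.

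**Working it through.** **Step 1. Compare the sections for one patient:** nerve pain or tenderness for under six months, normal muscle and sensory testing, no recurrent skin lesion.

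| Protocol section | Nature of the text | Result for this patient |
|---|---|---|
| Determining the eligibility for the study | study definition of neuritis | has neuritis |
| Definitions, neuritis | same list, any item is enough | has neuritis |
| Inclusion Criteria | formal criterion | eligible, if the neuritis is acute |
| Flow Chart for Recruitment | entry condition | no path to registration |
| Identification of eligible patients | case-finding before screening | not flagged |
| Definitions, acute neuritis | how onset is dated | onset cannot be dated unless earlier testing helps |

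The firm contradiction is between the first three rows and the fourth. The last two rows point the same way but carry less weight.

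**Step 2. Who has nothing to gain on recovery.** *Definitions* calls a muscle impaired at a score of four or less on a 0 to 5 scale. A patient at 5 throughout cannot gain a point, and a patient with a full sensory score cannot gain two. This covers two groups:

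- patients with pain, paraesthesia or tenderness and full scores;
- patients entered for recurrent skin lesions without neuritis, if their scores are full. Every section admits this group, so their entry is not in dispute, but they meet the same ceiling.

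Both groups can lose points, so both can show recurrence.

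**Step 3. Size of the dilution.** The Protocol gives no figure on this point to reproduce. Its sample size does reproduce, 2 × [(1.96 + 0.842) × 2 / 1]² = 62.8, or 63 per group. It rests on a combined skin, sensory and motor score, however, and does not measure an effect on recovery proportions.

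Inputs:

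- recovery among patients with a deficit, *p* = 60%, the lower end of the 60% to 70% improvement in nerve function cited in *Background*;
- share of randomised patients with full scores at baseline, *f*. The documents do not give it; 10% to 30% is assumed.

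Formulas, with *f* equal across arms and full-score patients counted as not recovered:

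- apparent recovery = *p* × (1 − *f*)
- apparent difference between arms = true difference × (1 − *f*)

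| *f* (assumed) | *p* = 60% | *p* = 70% | Part of the true difference kept |
|---|---|---|---|
| 10% | 0.60 × 0.90 = 54% | 0.70 × 0.90 = 63% | 90% |
| 20% | 0.60 × 0.80 = 48% | 0.70 × 0.80 = 56% | 80% |
| 30% | 0.60 × 0.70 = 42% | 0.70 × 0.70 = 49% | 70% |

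**The case against.** Much can be said in the plan's favour.

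- **The written criteria may be meant to govern.** The eligibility section defines neuritis expressly for this study. *Randomization* has the medical officer check the patient against the inclusion and exclusion criteria, so the local decision is not free discretion. The chart's abbreviation may be shorthand, and its arrows are lost in the text at hand. This makes one reading more likely. It does not remove the conflict, because the chart sets its own entry condition and no section ranks the two.
- **Two of the narrower sections are weak evidence.** A reader might infer that the flagging rule and the definition of acute neuritis make the pain-only patient ineligible. They do not say so. Flagging is a fast track to screening and does not exclude unflagged patients. The clause on acute neuritis dates onset and sits directly below the broad definition. What stands is that neither provides a route for this patient.
- **Pain alone does not mean full scores.** Such a patient may carry older impairment, or sensory changes below the Protocol's threshold for impairment that could still improve. The ceiling therefore applies to patients with full scores, not to everyone who enters through pain.
- **The denominator could be set in an analysis plan.** That is so for the analysis. It is not so for the entry rule, which acts at enrolment: no later document recovers patients whom a hospital never screened.

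**Conclusion.** The point holds as an inconsistency in eligibility with a consequence for the first primary outcome. The eligibility section, the inclusion criterion and the definition of neuritis admit a patient whom the recruitment flow chart does not. The result is a population that can differ by hospital and a recovery comparison that can be diluted.

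The size is illustrative. Across assumed shares of 10% to 30%, a 60% recovery rate appears as 54% to 42%, and 90% to 70% of a true difference between arms remains. This assumes equal shares across arms and that patients without a deficit count as non-recoveries.

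Three stronger conclusions are tempting, and the documents do not support them:

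- *Bias between arms.* Eligibility is settled before randomisation in a double-blind trial, so these patients are balanced in expectation.
- *Patients who contribute nothing.* They can show recurrence, the other primary outcome.
- *A gap between hospitals as large as a treatment effect.* With none of these patients at one hospital and 20% at another, 60% would sit beside 48%. That 12-point gap rests on a single assumed share, is not a difference between arms, and has no stated treatment effect on recovery to be compared with.

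**What to change.** 1. Reconcile *Identification of eligible patients*, *Determining the eligibility for the study*, *Inclusion Criteria*, the *Flow Chart for Recruitment* and *Definitions* to a single entry rule. Whether pain, paraesthesia or tenderness alone is enough is for the sponsor to decide. If it is, the rule must also say how onset is dated when there is no sensory or motor loss.
2. In *Primary outcomes* and *Statistical analysis*, state that recovery of nerve function is analysed among all randomised patients with motor or sensory impairment at baseline, by the Protocol's own definitions, and that recurrence is analysed in all randomised patients. Both analyses keep patients in their randomised arm. The restriction also covers patients entered for skin lesions who have no deficit.

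**Cost.** A short amendment to the text and the chart. The recovery analysis has a smaller denominator: of the 78 patients planned per arm, about 70, 62 or 55 would remain at shares of 10%, 20% or 30% (78 × 0.90 = 70.2; 78 × 0.80 = 62.4; 78 × 0.70 = 54.6), before attrition. Those removed with full scores could not have counted as recovered. Some patients with sensory changes below the impairment threshold would be removed as well, and that is a real though unquantified loss.

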#### Inclusion Criteria:

Patients with acute (< 6 months) neuritis with or without accompanying type 1 reaction or recurrent reactional skin lesions without neuritis.

#### Exclusion criteria

- Age less than 15 yrs
- Weight less than 30 kgs
- Confirmed Pregnancy (based on the LMP + Pregcolor strip test)
- Patient on treatment for Tuberculosis.
- Patients with known HIV sero-positivity.
- Patients with Hepatic dysfunction as evidenced by recent history of jaundice and abnormal LFTs on laboratory testing.
- Patients with pre-existing bone marrow dysfunction as evidenced by, abnormal counts, spleenomegaly or on examination.
- Patients with Hypertension (Sustained Diastolic Blood Pressure greater than 90 mm Hg) and Diabetes (Fasting Blood Sugar greater than 110mg/dl or random blood sugar greater than 200 mg/d) are not to be immediately included in the study. However once the condition is brought under control by appropriate medications, they can be included in the study provided they fulfil other criteria.
- Patients unable to comply with monitoring and follow up requirements.
- Patients presenting with Type 2 reactions.

#### Exclusion criteria

- Age less than 15 yrs
- Weight less than 30 kgs

.

#### TABLE 1

#### Exclusion criteria

- Age less than 15 yrs
- Weight less than 30 kgs
- Confirmed Pregnancy (based on the LMP + Pregcolor strip test)
- Patient on treatment for Tuberculosis.
- Patients with known HIV sero-positivity.
- Patients with Hepatic dysfunction as evidenced by recent history of jaundice and abnormal LFTs on laboratory testing.
- Patients with pre-existing bone marrow dysfunction as evidenced by, abnormal counts, spleenomegaly or on examination.
- Patients with Hypertension (Sustained Diastolic Blood Pressure greater than 90 mm Hg) and Diabetes (Fasting Blood Sugar greater than 110mg/dl or random blood sugar greater than 200 mg/d) are not to be immediately included in the study. However once the condition is brought under control by appropriate medications, they can be included in the study provided they fulfil other criteria.
- Patients unable to comply with monitoring and follow up requirements.
- Patients presenting with Type 2 reactions.

All patients found eligible will be invited to participate in the study. They will receive a detailed information sheet about the Aza study (in the local language); a patient counselor will help them understand the details of the study. They will be advised to return to the study MO after having fully understood these details; they will then give signed informed consent to participate in the study in the presence of the study MO, and will finally be included.

Patients who are either ineligible for trial entry or who do not wish to participate are treated as per the routine practice in that hospital.

